### Ethics and Dissemination

This is a multisite trial and follows National Institutes of Health guidelines to establish and operate within a single institutional review board (IRB) for final study monitoring. All research personnel will complete certification in responsible conduct of research, good clinical practice, and safe handling of biological samples. To minimize risk for participating families, we will inform all potential families of the purpose, procedures, and amount of time required to participate in the trial. We will minimize risk of breach of confidentiality by using a Health Insurance Portability and Accountability Act (HIPAA)-compliant telehealth platform and reviewing a group confidentiality agreement at the first session. We will minimize the risk of child pain or emotional discomfort when collecting blood samples by allowing families to use their own lancet and/or coordinating the sample collection to occur just after a clinic-based finger stick. Finally, we will protect caregivers by reviewing their responses on the study surveys within 24 hours of completion and contacting those who report concerning levels of depressive or anxiety symptoms to provide information on treatment resources. The trial was registered at ClinicalTrials.gov [NCT03914547].

The REDCHiP intervention builds on our previous research examining fear of hypoglycemia in caregivers of young children with T1D and fills a critical gap in behavioral intervention research in these understudied families. Moreover, the group-based telehealth approach is relatively novel for pediatric T1D interventions and may be easily scalable if the trial results confirm efficacy. We plan to disseminate the results of this trial to the pediatric diabetes community and broader medical community through national and international presentations at relevant scientific meetings and peer-reviewed manuscripts. We believe that there will be greater use of telehealth to deliver behavioral treatments for families of youth with T1D in the future because of the increasing adoption of telemedicine parity laws across the United States [57] and increased affinity for technology-enabled solutions to common needs in younger generations [58], including the need for convenient health care access [59]. We believe the format and general content of REDCHiP may be amenable to caregivers of older youth with T1D who also struggle with fear of hypoglycemia. Last, we expect that REDCHiP is in line with initiatives from the National Institute of Diabetes and Digestive and Kidney Diseases, which call for the development of more family-centered, efficacious, cost-effective, and easily scalable behavioral health interventions [60].

### Participants

For this randomized clinical trial, we will recruit 180 families of young children with T1D. Inclusion criteria are child aged from 2 to 5.99 years, T1D diagnosis ≥6 months, and use of an intensive insulin regimen (eg, insulin pump or multiple daily injections). Exclusion criteria are caregivers of children on a conventional insulin regimen, children who have an allergy or sensitivity to the adhesive and/or skin preparation used for a CGM, children with a comorbid chronic condition (eg, renal disease), and caregivers who do not speak English.

### Recruitment

We will recruit into the study at least one caregiver (mother, father, or guardian) who is primarily involved in the child’s daily T1D management. Each site will apply standardized recruitment procedures approved by a single IRB to achieve the target sample. We will use a combination of in-clinic and telephone recruitment. Families who express interest in participating via telephone will complete IRB-approved telephone informed consent procedures including an approved eConsent developed in the Research Electronic Data Capture (REDCap) system [61,62]. Families recruited in person may complete an eConsent or standard paper consent.

### Randomization

This study will use a 2-arm randomized attention control design with 90 families recruited to each of the REDCHiP and attention control intervention conditions. We will stratify caregivers based on their child’s sex, child age (2 to 3 years versus 4 to 5 years) and CGM use (CGM or no CGM) and randomize to condition using blocks of eight. Recruitment and randomization will occur simultaneously across all participating sites using site-specific randomization envelopes prepared by the study biostatistician. This strategy will allow us to populate groups using caregivers from any site, thereby improving our recruitment efficiency and minimizing possible clinic effects.

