**Methods:**

We created the Reducing Emotional Distress for Childhood Hypoglycemia in Parents (REDCHiP) intervention by merging age-appropriate T1D education and behavioral parenting strategies with cognitive behavioral therapy strategies that are effective for reducing fear and promoting adaptive coping. REDCHiP uses 10 video-based telehealth sessions that are a combination of group and individual sessions. We will recruit up to 180 families of young children with T1D to participate in this clinical trial from two pediatric diabetes clinics located in the midwestern and southern United States. Once families have been enrolled, we will randomize caregivers based on child age (age 2-3 years or 4-5 years), child sex, and family CGM use to participate in the REDCHiP or attention control intervention. Families will complete 3 assessment visits that coincide with study entry, end of treatment, and 3-month posttreatment. At each assessment visit, we will collect questionnaire data from caregivers, accelerometry data from caregivers and children, CGM data from children, and a blood sample to measure glycated hemoglobin levels from children.

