## Results

Recruitment began in July 2019, and enrollment is ongoing. The first wave of the intervention began in December 2019. We anticipate completing enrollment in 2023. Final reporting of results will occur within 12 months of the primary completion date.

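### A single block size of eight, published during enrollment, would make about 14–17% of allocations certain in advance if recruiting staff can see earlier assignments

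*Protocol article*

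**What the plan says.** The Randomization section of the protocol article sets a two-arm design "with 90 families recruited to each of the REDCHiP and attention control intervention conditions". It fixes these features:

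- **Strata:** "We will stratify caregivers based on their child’s sex", together with "child age (2 to 3 years versus 4 to 5 years) and CGM use (CGM or no CGM"). That is three two-level factors.
- **Block size:** one value, "randomize to condition using blocks of eight".
- **Vehicle:** "site-specific randomization envelopes prepared by the study biostatistician".

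The abstract (Methods) says families come "from two pediatric diabetes clinics located in the midwestern and southern United States". The Study Visit Procedures section puts informed consent first, then randomization, then visit 1. The Results section reports that "Recruitment began in July 2019, and enrollment is ongoing" and expects enrollment to finish in 2023. The Recruitment section describes "an approved eConsent developed in the Research Electronic Data Capture (REDCap) system", with paper consent as an alternative for families recruited in person.

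The article does not state who keeps or opens the envelopes, whether recruiting staff see earlier assignments, or who is masked.

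**The concern.** With one known block size, anyone who can see the assignments already made in a list can count them. Once four families in a block have gone to one arm, every remaining place in that block is known. Publishing the size during recruitment removes the last thing an observer would have to guess.

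A clinic may well know a child's sex, age and CGM use before approaching the family, so the relevant list could be identified in advance (an inference). In-clinic and telephone recruitment leaves some discretion over whom to approach and when. Randomizing after consent does not close this route, because the discretion is exercised before consent.

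At stake is comparability of the arms at entry. Parenting stress and fear of hypoglycemia are caregiver questionnaires, and a difference between arms in something unmeasured, such as motivation, would not be removed by adjusting for visit 1 scores.

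**Working it through.** **Inputs.** Block size 8, 1:1 allocation, 180 families, 2 × 2 × 2 = 8 strata (Randomization); 2 clinics (abstract); 20% attrition and 144 completers (Power Analysis).

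**The plan's own figure.** 144 / (1 − 0.20) = 180, which reproduces the recruitment target. The article gives no predictability figure.

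**One completed block.** A 4:4 block has C(8,4) = 70 equally likely orderings. An allocation is certain when it and all later places in the block belong to one arm. With r places left, including the current one, the probability is 2 × C(8 − r, 4) / 70:

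| Place in block | r | Probability certain |
|---|---|---|
| 1–4 | 5–8 | 0 |
| 5 | 4 | 2/70 = 2.9% |
| 6 | 3 | 10/70 = 14.3% |
| 7 | 2 | 30/70 = 42.9% |
| 8 | 1 | 70/70 = 100% |

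The sum is 112/70 = 1.6 of 8, or 20%. The closed form 2m/(m + 1) with m = 4 agrees. Always guessing the arm with more places left is right 5.33 times in 8 (67%).

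**Whole trial, separate lists per site.** 8 strata × 2 sites = 16 lists, averaging 180/16 = 11.25 families. If they are equal, 12 lists have 11 and 4 have 12. Each completes one block and then uses only places 1–3 or 1–4 of the next, where nothing is certain. Certain allocations: 16 × 1.6 = 25.6, and 25.6/180 = 14.2%. Simulation with unequal strata and sites (assumed CGM share 50–90%, site split 50–70%) gives 14.3–15.6%.

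**Whole trial, if sites shared the lists.** 8 lists, four of 22 and four of 23 families.
- List of 22: 2 × 1.6 + 0.029 + 0.143 = 3.37
- List of 23: 3.37 + 0.429 = 3.80
- Total: 4 × 3.37 + 4 × 3.80 = 28.7, and 28.7/180 = 15.9%

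Unequal strata give about 17%. The overall range is therefore 14–17%.

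**Effect of varying the size.** Simulated lists of 11 and 22 families, with an observer who knows the possible sizes but not their order. The sizes are illustrative assumptions.

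| Block sizes | Certain | Best guess correct |
|---|---|---|
| 8 only | 15% | 63–65% |
| 4, 8 | 5–6% | 65–67% |
| 4, 6, 8 | 2–2.5% | 66–67% |
| 6, 8, 10 | 2–2.5% | 64–65% |

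Certainty falls sharply. Guessing accuracy does not fall.

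**Effect of switching partway.** These gains are for lists that use mixed sizes from the first place. If an open first block of eight runs out, its 1.6 certain allocations remain. In a list of 11 they are all there are (1.6/11 = 14.5% before and after). In a list of 22, the other 14 places at 2–6% add 0.3 to 0.8, so (1.6 + 0.3)/22 to (1.6 + 0.8)/22 is about 9–11%, against 3.37/22 = 15.3% under fixed eights.

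**The case against.** A reader might infer that the trial is unmasked, that recruiters hold the envelopes, and that one in seven allocations therefore is predictable. The article supports none of these. It says the biostatistician prepares envelopes specific to each site and is silent on custody, sealing, separation of roles and masking. A condensed article may leave such details to the full protocol, so the silence is not itself a fault.

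The practical obstacles are also real. With 11.25 families per list between July 2019 and some point in 2023 (3.5 to 4.5 years), a list gains about 2.5 to 3.2 families a year, so a block of eight takes about 2.5 to 3.2 years to fill. Most of the certainty sits in places 7 and 8. Using it means tracking up to 16 slow lists and acting before consent.

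Nor are all outcomes exposed in the same way. Caregiver sleep is partly measured by accelerometer, HbA1c comes from a central laboratory, and glucose from a sensor. An imbalance in fear or stress could be seen at visit 1 and is in the outcome model, although visit 1 follows randomization and is not a clean pre-allocation measure. Finally, a block of eight is already better than a block of four, where 33% of places are certain.

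All of this stands, and it limits the size of the problem. It does not touch the core: the single size and its disclosure are stated choices, not omissions, and both can be improved.

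**Conclusion.** The point holds as a minor, conditional weakness. If recruiting staff can see earlier assignments in a list, about 14–17% of the 180 allocations (roughly 26 to 31 families) would be certain before the family is approached. The lower end assumes 16 separate lists of equal size; the upper end assumes 8 shared lists of unequal size. If recruiting staff cannot see earlier assignments, the figure does not apply.

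The realised bias is probably small. The documents do not show that any allocation was foreseen, that the trial is unmasked, or that an imbalance in fear would go undetected. Unmeasured differences such as motivation are what the planned adjustment would not reach.

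**What to change.** For the allocations that remain:

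1. Let blocks already open run to completion.
2. Have the biostatistician generate the rest of each list with randomly varied block sizes, in the same site, sex, age and CGM strata.
3. Keep the sizes from recruiting staff and out of documents they see.
4. Release each assignment only after consent, centrally if the existing REDCap system supports it. The article describes REDCap for consent and surveys, not for randomization, so this needs checking.
5. State whether recruiting staff can see earlier assignments. If they cannot, saying so would largely resolve the point.

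Step 2 brings certain allocations to about 2–6% in lists not yet started and helps less in lists already under way. For open blocks, whose size is already public, the protection comes from keeping earlier assignments from recruiters. No choice of sizes removes guessability, which stays at about 64%.

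The cost is a short amendment and regenerated lists. Arm imbalance within a small stratum could be slightly larger if a size above eight is used: at most half a block, so 5 with ten against 4 with eight.

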### Study Visit Procedures

After informed consent and randomization, all families will complete study visit 1, during which caregivers will complete online surveys in REDCap and we will show caregivers (via a short video) how to place the research-grade accelerometer on their child’s nondominant wrist (to measure child physical activity) or ankle (to measure child sleep) and how to place the accelerometer on their own nondominant wrist to measure caregiver sleep. We will also teach caregivers how to upload glucometer and insulin pump data from home to a central study database using a commercially available data aggregating system (Glooko). In cases where caregivers cannot use the data aggregating system because of problems with device compatibility, we will collect .csv files. To measure children’s daily glucose levels, we will place a FreeStyle Libre Pro (Abbott Laboratories) CGM sensor on the child’s upper nondominant arm. We will collect a finger stick blood sample from children using a reliable mail-in kit to measure a baseline HbA_1c_ level. Finally, we will determine if caregivers need to borrow any equipment to participate in the intervention (eg, web camera, microphone, or tablet). After study visit 1, caregivers will begin participating in video-based telehealth sessions according to their group assignment (eg, REDCHiP or attention control intervention). Caregivers will participate in 10 video-based telehealth sessions administered during 13 weeks via a HIPAA-compliant telehealth platform that permits multiparticipant video teleconferencing so that each caregiver can both see and hear other caregivers. During weeks 14 to 15 of the trial, all families will engage in study visit 2 to complete posttreatment surveys online, collect accelerometry data from children and caregivers, collect child CGM data and finger stick blood sample to measure child HbA_1c_, and recover any loaned study-related devices. Approximately 12 weeks after study visit 2, all families will complete study visit 3, which will involve final data collection: online surveys, child CGM data, and a finger stick blood sample to measure child HbA_1c_ (Figure 2 and Table 3).

Of note, the study protocol will enable families to complete study visits either in their home, at the diabetes clinic, or at another location (eg, library). Additionally, our protocol includes strategies to retain families in the study in the rare event that they move away (eg, telehealth, online surveys, mail-in HbA_1c_ kits) or recruit families who self-refer based on word of mouth or ClinicalTrials.gov. All participating caregivers and children will receive compensation for study visits 1 through 3. As needed, the study will use prepaid postage boxes for families to return study-related devices (eg, accelerometers and CGM sensors) to further reduce the burden on participating families.

**Figure 2 figure2:**
[figure not shown]
Participant timeline.

**Table 3 table3:** Study outcome measures.

Outcome		Measure	Assessment schedule
**Child**			
	T1D^a^ treatment and history	Collect demographics; caregivers complete T1D History Questionnaire including caregiver report of family/child demographics, child insulin regimen, CGM^b^ use, and history of T1D complications	Visit 1
	Child physical activity	Calculate daily moderate to vigorous physical activity and sedentary time based on age-specific cutoffs using accelerometer data	Visits 1, 2
	Sleep	Calculate TST^c^, sleep latency, and sleep efficiency (TST/total time in bed); caregivers complete online sleep log to verify child sleep versus periods of wakeful inactivity	Visits 1, 2
	Glycemic control	Collect children’s blood samples using a finger stick capillary sampling kit (with or without mail-back box) developed at one of the study sites and record hemoglobin A_1c_; we will send samples to a central laboratory for processing using an automated G8 Analyzer^d^ with a reference range of 4.0% to 6.0%; this method has demonstrated reliability with a correlation of 0.98 relative to fresh venous samples	Visits 1, 2, 3
	Glucose variability	Calculate percentage above, below, and within target range (target: 70 to 180 mg/dL) and mean and standard deviation of daily glucose using FreeStyle Libre Pro^e^ data	Visits 1, 2, 3
	Child treatment engagement	Calculate frequency of self-monitoring blood glucose and mealtime (bolus) insulin use [63] using device data (eg, glucometer and insulin pump)	Visits 1, 2, 3
**Caregiver**			
	Hypoglycemia fear	Calculate total, worry, and behaviors scores from the HFS-PYC^f^ [15,26]	Visits 1, 2, 3
	Parenting stress	Calculate stress frequency and stress difficulty scores from the PIP^g^ [64]	Visits 1, 2, 3
	Depressive symptoms	Calculate total score from the CES-D-R^h^ [65]	Visits 1, 2, 3
	Anxiety	Calculate total score from PROMIS-A^i^ [66]	Visits 1, 2, 3
	Psychopathology	Calculate the depression, anxiety, and somatization scores and the Global Severity Index from the BSI-18^j^ [67]	Visits 1, 2, 3
	Sleep	Calculate TST, sleep latency, and sleep efficiency (TST/total time in bed) using accelerometer data; caregivers will also complete an online sleep log and the PROMIS-S^k^ [68], and we will calculate total score	Visits 1, 2 (Visits 1, 2, 3 for PROMIS-S)
	Treatment satisfaction	Calculate total score from the Treatment Satisfaction Questionnaire	Visit 2

^a^T1D: type 1 diabetes mellitus.

^b^CGM: continuous glucose monitor.

^c^TST: total sleep time.

^d^G8 analyzer: G8a High-Performance Liquid Chromatography Hemoglobin A_1c_ Analyzer (Tosoh Bioscience Inc).

^e^FreeStyle Libre Pro: FreeStyle Libre Pro Flash Glucose Monitoring System (Abbott Laboratories).

^f^HFS-PYC: Hypoglycemia Fear Survey–Parents of Young Children.

^g^PIP: Pediatric Inventory for Parents.

^h^CES-D-R: Center for Epidemiological Studies–Depression Scale Revised.

^i^PROMIS-A: Patient-Reported Outcomes Measurement Information System–Anxiety short form.

^j^BSI-18: Brief Symptom Inventory–18.

^k^PROMIS-S: PROMIS Sleep Disturbance and Sleep-Related Impairment.

### Data Analysis Plan

We will measure parenting stress and caregiver fear of hypoglycemia using the Pediatric Inventory for Parents [64] and the Hypoglycemia Fear Survey–Parents of Young Children [15,26], respectively. We will use child HbA_1c_ levels and percentage of time in range (eg, 70 to 180 mg/dL) to examine child glycemic control and glycemic variability, respectively. To test for treatment outcomes, we will model study visit 2 scores as a function of visit 1 scores, condition (REDCHiP versus attention control intervention), and selected covariates (eg, race/ethnicity, pump use) in mixed models that include a random intercept to account for clustering of participants within group cohorts. We will accommodate nonnormal outcome variables with log transformation, modeling with an appropriate generalized mixed model or nonparametric test. We will test the effect of condition based on whether the 95% confidence interval for the condition coefficient includes zero (equivalent to a 2-sided test at α=.05). To determine long-term treatment effects, we will test for sustained improvement on outcome variables by modeling scores at study visit 3 as a function of visit 1 scores and condition (REDCHiP versus attention control intervention). To control the overall rate of type I errors, we will conduct these analyses only for variables with a statistically significant condition effect in our primary analysis of treatment outcomes.

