Up to 60% of caregivers of young children with T1D report fear of hypoglycemia, which directly affects caregiver psychological and emotional well-being [15]. Additionally, in young children with T1D, caregivers may perceive hypoglycemia as unpredictable, exacerbating their level of fear [16]. Building on past research, we developed a theoretical model for caregiver fear of hypoglycemia (Figure 1) which identifies child and caregiver variables that may underlie caregiver fear of hypoglycemia. For example, we have data suggesting that a child’s T1D history, including past experience with hypoglycemia, and a child’s sleeping behavior may relate to caregiver fear of hypoglycemia [15,17,18]. In addition, in older youth with T1D, there is evidence that child physical activity levels relate to caregiver fear of hypoglycemia [19-22].

For caregiver variables, several studies suggest that T1D-related distress, parenting stress, caregiver depressive and anxiety symptoms, and decreased caregiver sleep may exacerbate their perceptions of fear of hypoglycemia [23-27]. Our theoretical model of caregiver fear of hypoglycemia then proposes that greater caregiver fear of hypoglycemia relates to hypoglycemia avoidance behaviors, including maintaining blood glucose levels above the recommended range, treating blood glucose levels that are within the target range, and delaying or reducing insulin doses [16,28]. Our theoretical model of caregiver fear of hypoglycemia suggests that when caregivers engage in more hypoglycemia avoidance behaviors, these maladaptive coping strategies lead to chronically higher blood glucose levels, more glycemic variability, and increased risk for T1D-related complications for children [29,30]. Thus, our model suggests that caregiver fear of hypoglycemia may function as a barrier to optimal glycemic control and should be a target of behavioral interventions for families of young children with T1D.

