### Objectives

The aims of this randomized clinical trial are to (1) evaluate whether caregivers who receive the REDCHiP intervention report reductions in parenting stress and fear of hypoglycemia immediately posttreatment compared with caregivers who receive the attention control intervention; (2) evaluate whether children of caregivers who receive the REDCHiP intervention have lower HbA_1c_ and less glycemic variability posttreatment compared with children of caregivers who receive the attention control intervention; and (3) examine whether maintenance reductions in parenting stress and caregiver fear of hypoglycemia and child HbA_1c_ occur 3 months’ posttreatment for families receiving the REDCHiP intervention. Based on preliminary data, our primary hypotheses are (1) caregivers who receive REDCHiP will report reductions in parenting stress and fear of hypoglycemia compared with caregivers who receive the attention control intervention and (2) children of caregivers who receive REDCHiP will achieve more optimal glycemic control than children of caregivers who receive the attention control intervention.

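### Time in range is the only variable named for glycemic variability, but it mixes glucose level with spread and cannot by itself show Aim 2's reduction in variability

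*Protocol article*

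**What the plan says.** Aim 2 (Objectives) is that children in the REDCHiP arm will "have lower HbA_1c_ and less glycemic variability posttreatment" than children in the attention control arm. HbA1c and variability are two targets there. The theoretical model in the Background also keeps level and variability apart: avoidance behaviors "lead to chronically higher blood glucose levels, more glycemic variability, and increased risk for T1D-related complications for children".

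The Data Analysis Plan then assigns one variable to each construct. HbA1c and "percentage of time in range (eg, 70 to 180 mg/dL) to examine child glycemic control and glycemic variability, respectively" are the measures, and the last word of that phrase ties HbA1c to control and time in range to variability. No measure of dispersion is named in that section. The condition effect is judged by whether the "95% confidence interval for the condition coefficient includes zero (equivalent to a 2-sided test at α=.05").

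Table 3 is broader. Its glucose variability row, scheduled at visits 1, 2 and 3, reads: "Calculate percentage above, below, and within target range (target: 70 to 180 mg/dL) and mean and standard deviation of daily glucose", from the study's own sensor.

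**The concern.** Time in range is the share of readings between 70 and 180 mg/dL. It changes when the whole distribution shifts and also when the distribution narrows or widens about a fixed mean. A between-arm difference in it does not say which of the two happened.

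Two misreadings follow. First, if the intervention lowers mean glucose, as the HbA1c half of Aim 2 expects, time in range can rise with no change in spread, and the plan would record this as less variability. The two halves of Aim 2 would then partly reflect the same change. Second, if mean glucose lies near or above the upper limit of 180 mg/dL, a real narrowing of spread can leave time in range almost unchanged, or lower it, because fewer readings dip back into range.

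The choice also carries forward. Visit 3 scores are modelled only for variables with a significant condition effect at visit 2, so the variable chosen for variability decides whether that construct is followed up.

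**Working it through.** The plan gives no figure on this point to reproduce. The check is how time in range (TIR) responds when level and spread are changed one at a time.

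**Inputs**
- Range limits 70 and 180 mg/dL: Data Analysis Plan and Table 3.
- Mean and SD of sensor glucose: not in the documents. Assumed means are 150 to 220 mg/dL and assumed SDs are 40 to 90 mg/dL.
- Shape of the readings: assumed. Normal and lognormal are both shown.

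**Formulas**
- Normal: TIR = Φ((180 − mean)/SD) − Φ((70 − mean)/SD).
- Lognormal, matched on mean and SD: s² = ln(1 + (SD/mean)²), m = ln(mean) − s²/2, TIR = Φ((ln 180 − m)/s) − Φ((ln 70 − m)/s).
- CV = SD/mean.

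**Step 1. Level changes, SD fixed at 60 mg/dL**

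Worked normal case:
- Mean 210: Φ(−0.500) − Φ(−2.333) = 0.3085 − 0.0098 = 29.9%.
- Mean 150: Φ(0.500) − Φ(−1.333) = 0.6915 − 0.0912 = 60.0%.

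| Mean (mg/dL) | TIR, normal | TIR, lognormal |
|---|---|---|
| 210 | 29.9% | 34.1% |
| 190 | 41.1% | 49.1% |
| 170 | 51.8% | 62.5% |
| 150 | 60.0% | 71.0% |

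The SD is the same in every row, yet TIR roughly doubles.

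With the CV fixed at 40% instead, lowering the mean from 200 to 170 raises lognormal TIR from 46.2% to 61.6%. Relative spread is unchanged here, although the SD falls from 0.40 × 200 = 80 to 0.40 × 170 = 68 mg/dL.

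**Step 2. Spread falls, mean fixed**

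| Mean (mg/dL) | CV change | SD change (mg/dL) | TIR, normal | TIR, lognormal |
|---|---|---|---|---|
| 150 | 40% to 30% | 60 to 45 | 60.0% to 71.0% | 71.0% to 77.2% |
| 170 | 40% to 30% | 68 to 51 | 48.8% to 55.3% | 61.6% to 63.2% |
| 190 | 40% to 30% | 76 to 57 | 39.0% to 41.3% | 51.3% to 48.5% |
| 200 | 40% to 20% | 80 to 40 | 34.9% to 30.8% | 46.2% to 33.3% |
| 220 | 41% to 23% | 90 to 50 | 28.1% to 21.1% | 37.4% to 21.7% |

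With the mean well inside the range, less spread gives more time in range, as the plan presumes. At a mean of 170 the lognormal response has almost gone. At 190 the sign depends on the shape of the distribution. At 200 and 220, for the changes shown, it is reversed under both shapes.

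**The case against.** The strongest defense has four parts.

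- **Time in range does carry information on spread.** This stands. At a mean of 150, a fall in CV from 40% to 30% raises it under both shapes. A reader might infer that it measures level and not variability at all. That goes too far, because it reflects both.
- **Table 3 already lists the SD.** The row "Calculate percentage above, below, and within target range (target: 70 to 180 mg/dL) and mean and standard deviation of daily glucose" makes it a declared outcome measure, and a condensed article may leave a fuller outcome list to an analysis plan not shown. So a reader who infers that variability will go untested has gone beyond the text. What remains is an express assignment in the Data Analysis Plan: it chooses time in range for variability and does not mention the SD. That is a stated choice, not an omitted detail.
- **The reversed sign is conditional.** This also stands. It needs a mean near or above 180 mg/dL and depends on the shape of the readings and the size of the change. At a mean of 190 with normal readings, a CV fall from 40% to 30% still raises time in range. The Background says that only 20% of young US children meet the HbA1c target, which suggests raised glucose but fixes no sensor mean. Halving the CV is also a large change to assume. It would be wrong to infer that the trial will report the wrong sign.
- **The fixed-CV example depends on preferring CV to SD.** That is fair, since the SD does fall in it. The fixed-SD comparison does not have this weakness and gives the same message.

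The consequence is also bounded. HbA1c and time in range are separate named outcomes, so a reader would see what was measured. Aim 1 and the power analysis are unaffected.

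**Conclusion.** The point holds as one of measure and label. The Data Analysis Plan fixes time in range as the sole named variable for glycemic variability, while Aim 2 and the Background treat variability as distinct from level. A difference in time in range cannot by itself support a claim of less variability.

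That conclusion follows from the definition of time in range and needs no assumed values. The sizes do need them. With a constant SD of 60 mg/dL, a fall in mean from 210 to 150 adds about 30 percentage points under normal readings (60.0 − 29.9 = 30.1) and 37 under lognormal (71.0 − 34.1 = 36.9). The muted or reversed response to less spread is a possibility tied to high mean glucose. The documents give no baseline mean or SD from which to say how likely it is.

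The point should be settled before analysis. It bears on the interpretation of one part of Aim 2, not on the design or the sample size.

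**What to change.** In the Data Analysis Plan, name the SD of sensor glucose already listed in Table 3 as the Aim 2 variability outcome at visit 2. The CV is an acceptable alternative, since both of its components are in the same Table 3 row. It has the advantage of staying constant when mean and SD move in proportion, but the SD alone would meet the concern. Describe time in range as a glycemic-control outcome beside HbA1c.

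The cost is one sentence. The sensor data, visit schedule, model and sample size stay as they are.
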